## Abstract

To evaluate the efficacy of acupuncture combined with rehabilitation training in patients with intensive care unit (ICU)-acquired muscle weakness (ICUAW), a single-blinded, randomized, sham-controlled clinical trial is designed for execution. In total, 56 participants with ICUAW will be randomly assigned to the treatment and control groups with 28 participants in each group. The participants will be treated with acupunctures or sham procedures at LI15, LI11, ST36, GB34, and ST31, 5 times per week for a total of 20 sessions in 4 weeks while they will receive rehabilitation training. Patients will be followed up every month for 3 months after treatment. The primary outcomes include changes in quadriceps femoris muscle area, thickness, vastus intermediate muscle thickness, subcutaneous tissue thickness, and ultrasonic intensities of the rectus femoris. The secondary outcomes consist of the modified Barthel index score and the Medical Research Council total score. Participants' mechanical ventilation, the rate of detachment at the second week, the 28-day survival rate, and the occurrence of adverse reactions will be measured, and any side effects will be reported and recorded. Patient outcomes between the treatment and control groups will be compared and statistically tested. We anticipate that the therapeutic regimen of acupuncture combined with rehabilitation training would be more effective than the rehabilitation training alone for the treatment of the ICUAW. The findings of this study could help develop a better strategy for the treatment of the ICUAW disease and explore a clinical application of an acupuncture technique. Trial registration: Chinese Clinical Trial Register ChiCTR2000038779. Registered 30 September, 2020, https://www.chictr.org.cn/showproj.aspx?proj=62284.

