## 1. Introduction

The intensive care unit (ICU)-acquired weakness (ICUAW) is a generalized muscle weakness complication developed during ICU admissions for which no other disease cause can be identified except for acute illness or its treatment. Approximately 40% of ICU patients with a history of at least 48 h of mechanical ventilation develop ICUAW. The disease affects peripheral and respiratory muscles, causing prolonged time of mechanical ventilation and hospital stay, increased hospital mortality, and chronic disability [1–5]. The mechanisms by which ICUAW develops are complex and involve functional and structural alterations in both the muscles and the nerves. Recovery from ICUAW typically takes several weeks or months, and muscle weakness in some patients can last for up to 2 years after discharge from the ICU. Because the pathogenesis of ICUAW is still unclear, there are no specific treatments. The current management of ICUAW includes an active treatment of the primary disease (e.g., sepsis), prevention of infection, control of high blood sugar, reduction of the duration of immobilization, and avoidance of other known risk factors, such as malnutrition, unnecessary application of corticosteroids and neuromuscular blockers, and early rehabilitation [6–8]. Thus, the development of easy-to-perform, more effective ICUAW-targeted interventions is needed for the prevention and treatment of ICUAW.

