### 2.2. Modified Barthel Index (MBI) Score and Medical Research Council (MRC) Total Score

#### 2.2.1. Inclusion Criteria

Participants who would meet all of the following criteria will be enrolled in the study: (1) age >18 years, male and female patients diagnosed with ICUAW; (2) those who were previously admitted to ICU for more than 24 h; (3) acute physiology and chronic health disease classification system II (APACHEII) scores in the range of 8–20 points calculated based on the 12 admission physiologic variables and patient's age and chronic health, as described by Knaus et al. [19]; (4) patients with stable hemodynamics; (5) patients with mechanical ventilation, oxygen concentration [fraction of inspired oxygen (FiO_2_)] < 0.6, and positive end-expiratory pressure (PEEP) < 10 cmH_2_O; and (6) patients who would either themselves and/or their families voluntarily agree to participate in the study and provide signed informed consent.

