### 2.12. Secondary Outcome Measures

The average change in quadriceps femoris muscle area, thickness, vastus intermediate muscle thickness, subcutaneous tissue thickness, and ultrasonic intensity of the rectus femoris will be measured, and the scores obtained at the baseline, 2 weeks, and 3 months after the last treatment will be compared. MBI and MRC scores will be evaluated at 2 weeks, 4 weeks, and 3 months after the last treatment. The participants' mechanical ventilation, rate of detachment at the second week, 28-day survival rate, and occurrence of adverse reactions will be evaluated, and any noticed side effects of the treatment will be recorded. All outcome readings will be scored on quantitative scales and presented as mean values and standard deviations.

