### 2.21. Efficacy Analysis

Efficacy data analyses will be conducted based on the intention-to-treat population. All participants will be initially included in one of the two groups and considered in the statistical analyses. Analysis of efficacy will be conducted for each protocol and include all the participants who would complete the entire research processing. Descriptive statistics will be used to report primary outcome indicators between the two groups. All the data will be statistically analyzed using SPSS. All measurements will be expressed as mean ± standard deviation. The *t*-test will be used for comparisons between two samples if the distributions are normal, and the F-test will be used for comparisons among multiple samples. The Kruskal–Wallis H-rank sum test was used if the distribution is not normal. The participants' sex and course of disease will be recorded, and the data will be tested using the *χ*^2^ test. The ultrasound data will be analyzed by a mixed-effect model. The Cox-regression analysis will be performed to identify outcome-related factors. *P* < 0.05 will be considered as statistically significant.

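### Secondary outcome of mechanical ventilation has no metric but is to be shown as mean and SD; read as time on the ventilator, it would count an early death as short ventilation

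*Protocol article*

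**What the plan says.** Section 2.12 (Secondary Outcome Measures) names three neighbouring items: "mechanical ventilation, rate of detachment at the second week, 28-day survival rate". The Abstract gives the same list: "Participants' mechanical ventilation, the rate of detachment at the second week, the 28-day survival rate". In both places ventilation stands apart from the week-2 detachment rate and from survival. Neither place says whether it is a duration, a count of ventilator-free days or a status.

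Section 2.12 then sets one rule for everything: "All outcome readings will be scored on quantitative scales and presented as mean values and standard deviations". Section 2.21 (Efficacy Analysis) repeats it: "All measurements will be expressed as mean ± standard deviation". For two groups, a t-"test will be used for comparisons between two samples if the distributions are normal", with a Kruskal–Wallis test otherwise. Cox regression also appears in 2.21, but only as an "analysis will be performed to identify outcome-related factors"; it is not tied to ventilation.

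Section 2.2.1 requires ventilation at entry: "patients with mechanical ventilation, oxygen concentration". The Introduction describes the disease as "causing prolonged time of mechanical ventilation and hospital stay, increased hospital mortality, and chronic disability", so deaths are to be expected, but no rate is given. Section 2.23 covers data that are not obtained, does not mention death, and announces a separate statistical analysis plan, which is not shown.

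**The concern.** Ventilation status at baseline carries no information, because all participants are ventilated, and being off the ventilator at week 2 is already its own outcome. What remains to be put on a quantitative scale and averaged is time on the ventilator. The Introduction and the Discussion also speak of ventilation in terms of its length.

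Time on the ventilator stops at weaning or at death, and a plain mean does not tell the two apart. A participant who dies on the ventilator on day 4 contributes 4 days; a survivor weaned on day 12 contributes 12. The worse outcome gets the better score. If the arms differ in early deaths, whether by a real effect or by chance, the ventilation comparison is pulled towards the arm with more of them. Correcting the analysis of the week-2 rate or of missing ultrasound scans would leave this untouched.

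**Working it through.** The plan states no figure for ventilation, so there is none to reproduce. The check has two parts.

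**1. Does anything in the article prevent an early death from scoring well?**

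- The t-test in 2.21 compares the means, so it takes over the distortion.
- The rank test in 2.21 orders the same numbers, and early deaths still rank as short.
- The Cox regression in 2.21 is for factors related to outcome, and no competing event is named.
- The missing-data rule in 2.23 is for data not obtained. Someone who dies on the ventilator has a recorded time, so the rule need not apply.
- The analysis of completers in 2.21 would drop the deaths and so compare only those who survive.
- 28-day survival is reported as its own outcome. That discloses a mortality difference but does not correct the ventilation result.

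**2. How large could the distortion be?**

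All inputs here are assumptions except the 28 per arm (Abstract):

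- time to weaning exponential with mean m = 10, 14 or 18 days, capped at 28, the same in both arms;
- mortality 15% in one arm, 25% or 35% in the other;
- death time D uniform on days 1 to 10;
- ventilation counted to weaning or death, whichever comes first.

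Formulas, with V the capped weaning time and Δp the excess mortality:

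- E[V] = m(1 − e^(−28/m))
- E[min(V, D)] = m(1 − G), where G = (m/9)(e^(−1/m) − e^(−10/m))
- Difference in mean ventilation days = −Δp × (E[V] − E[min(V, D)])
- Difference in ventilator-free days, death scored 0 = −Δp × (28 − E[V])

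| m | E[V] | E[min(V, D)] | Mean ventilation days, Δp = 0.10 / 0.20 | Ventilator-free days, Δp = 0.10 / 0.20 |
|---|---|---|---|---|
| 10 | 9.39 | 4.03 | −0.54 / −1.07 | −1.86 / −3.72 |
| 14 | 12.11 | 4.39 | −0.77 / −1.54 | −1.59 / −3.18 |
| 18 | 14.20 | 4.60 | −0.96 / −1.92 | −1.38 / −2.76 |

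Example, m = 14 and Δp = 0.20: 12.105 − 4.385 = 7.72 and 0.20 × 7.72 = 1.54 days shorter; 28 − 12.105 = 15.895 and 0.20 × 15.895 = 3.18 fewer ventilator-free days. The arm with more deaths looks better on the first measure and worse on the second.

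Simulation agrees with the table to within simulation error. It also gives the standard deviations, 7.2 to 9.7 days. With 28 per arm the standard error of the difference, √((SD₁² + SD₂²)/28), is 2.0 to 2.6 days, so the distortion is about 0.3 to 0.75 of a standard error. In the same simulation the chance that a random participant from the arm with more deaths has the shorter time is 0.52 to 0.56 instead of 0.50, so a rank test leans the same way.

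A second set of assumptions (deaths on days 1 to 14, mortality 10% against 20% or 30%, m = 10, 14 or 21) gives 0.4 to 1.9 days in the same direction.

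No true mortality effect is needed. With 28 per arm and equal mortality of 10%, 15% or 20%, the arms differ by three or more deaths (3/28 = 10.7 points) by chance in about 26%, 35% or 40% of trials.

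**The case against.** The strongest objection is that the article never says duration, never says that counting stops at death, and never says how a death is scored. A reader might infer that the protocol itself lays down that an early death counts as short ventilation; it does not. That step is an inference from universal ventilation at entry and the required mean and SD. This part of the objection stands, and the point is therefore conditional.

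Second, the sentence on means and SDs is loose. Taken literally it would also cover the detachment rate, the survival rate and adverse reactions, although Section 2.22 uses χ² or Fisher's exact test for adverse events. It may have been written with the ultrasound readings and scales in mind. That is fair, but it is the only summary the article gives for ventilation, and an analyst who follows it with ventilator days would get the distorted result.

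Third, the separate analysis plan may define ventilator-free days or treat death as a competing event. It may, and silence alone would not be a finding. Here, though, the protocol does fix a summary, and that summary is unsuitable under the most natural reading.

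Fourth, the distortion is small against the noise and would rarely produce a significant false benefit by itself. This also stands. A reader might conclude that the ventilation outcome cannot be interpreted at all; with survival reported beside it and a distortion below one standard error, that goes too far.

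Lastly, a reader might take shorter ventilation as a benefit the Introduction claims for acupuncture. The Introduction's sentence on prolonged ventilation describes harms of the disease. Its list of acupuncture benefits mentions a shorter offline time, which may refer to weaning but does not clearly say so.

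**Conclusion.** The point holds in conditional form. Section 2.12 names ventilation without a metric, fixes a mean-and-SD summary and gives no rule for deaths. If the measure is time on the ventilator, as is most natural, the comparison can lean towards the arm with more early deaths, and neither the t-test nor the rank test in 2.21 prevents this. With 10 to 20 points of excess early mortality and no effect on weaning, the lean is about 0.5 to 2 days, less than one standard error at 28 per arm; the opposite sign appears on ventilator-free days. The direction follows from counting days up to death. The size rests on assumed mortality and weaning times that the protocol does not supply. The problem does not arise if deaths are scored as a bad result. Severity is low to moderate: the outcome is secondary, and separate reporting of 28-day survival limits the harm without correcting the ventilation result.

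**What to change.** In Section 2.12, define the ventilation outcome so that death is not scored as a good result. One suitable definition is ventilator-free days from randomisation to day 28, with death by day 28 scored 0, compared by a rank-based method and shown as median and quartiles. Time to successful weaning, with death as a competing event, is an acceptable alternative. Exempt this outcome from the general mean-and-SD rule in 2.12 and 2.21. Show 28-day survival beside it, and give ventilation time among survivors as description only.

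The cost is mainly wording. 28-day vital status is already needed for the survival outcome. The date of weaning must be taken from the ICU record, since Table 1 has no row for ventilation and the week-2 rate needs only the status at that time. A small downside is that ventilator-free days combine death and ventilation in one number, so both components must be reported with it.

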### 2.13. Safety Assessment

Adverse events (AEs) are defined as events in which at least four participants suffer from the same symptom, including any undesirable experiences that may occur during the trial period. This may or may not be associated with the intervention. Participants will be instructed to report any AE to the research team at any time. All details of AE, including the time of occurrence, description of symptoms, duration of symptoms, severity, management measures, and causality to the intervention, will be recorded on case report forms (CRFs). The common AEs related to acupuncture, including local skin pain, itching, ulcers, leaving needles in participants, nausea during acupuncture, fainting during acupuncture, severe sharp pain, sharp pain lasting for more than 30 min, hematomas around the site of needling, bleeding, numbness, infection around the needle sites, sleeplessness after acupuncture, and dizziness after acupuncture, will be reported [20]. The causality between AEs and intervention will be assessed according to the World's Health Organization Uppsala Monitoring Center System for Standardized Case Causality Assessment [21]. In the event of AE occurrence, patients will be given an appropriate treatment until their conditions stabilize. Severe AEs will be reported to the safety monitoring board within 24 h.

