### 2.9. Discontinuation of the Intervention

The intervention will be terminated in cases with severe adverse events, when participants wish to withdraw from the trial, or when patients use unpermitted medication that would interfere with the recovery outcomes. Patients will have the option to ask the doctor about possible alternative therapies (e.g., nutritional support such as use of tricreatine *β*-hydroxyl-methylbutyrate, antioxidant therapy, and immunoglobulin therapy).

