### 2.22. Safety Analysis

According to the definition of AEs, AEs will be recorded in conjunction with their severity level, causes, and explanations. Moreover, the number and the rate of AE will be described statistically. If AEs would be required to be compared between groups, the *χ*^2^ test or the Fisher's exact test will be used for statistical analyses.

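### The protocol counts an adverse event only when four participants share a symptom, which contradicts its own per-event recording and leaves a harm in one to three participants without a clear 24 h or analysis route

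*Protocol article*

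**What the plan says.** Section 2.13 (Safety Assessment) defines the term: "Adverse events (AEs) are defined as events in which at least four participants suffer from the same symptom", and continues "including any undesirable experiences that may occur during the trial period". It adds that an AE need not be related to the intervention. The same section then asks for case report form (CRF) entries on "All details of AE, including the time of occurrence, description of symptoms, duration of symptoms, severity, management measures, and causality to the intervention", lists common acupuncture-related events that are to be reported, and sets the expedited rule: "Severe AEs will be reported to the safety monitoring board within 24 h".

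Section 2.22 (Safety Analysis) refers back to the definition: "According to the definition of AEs, AEs will be recorded in conjunction with their severity level, causes, and explanations". It adds that "the number and the rate of AE will be described statistically" and allows a chi-squared or Fisher's exact test between groups.

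Two other sections bear on the point. Section 2.12 (Secondary Outcome Measures) says "any noticed side effects of the treatment will be recorded" and includes 28-day survival. Section 2.9 (Discontinuation of the Intervention) says "The intervention will be terminated in cases with severe adverse events". No definition of a severe or serious event that is free of the four-participant condition appears anywhere in the article.

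**The concern.** An AE is normally a property of one participant at one time. Here it becomes a property of a group: whether an event qualifies depends on how many other participants have had the same symptom. This has two consequences.

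- **It cannot be applied as events happen.** Recruitment runs from October 2020 to September 2023. When the first, second or third case occurs, nobody knows whether a fourth will follow. A 24 h clock cannot start on an event whose status is not yet known.
- **It carries into the analysis.** Section 2.22 ties its summary to the definition, so the AE number, rate and any group comparison could omit symptoms seen in three or fewer participants.

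The participants are mechanically ventilated ICU patients, the Discussion names safety as an aim, and the trial has only 28 patients per arm. Several of the listed events, such as a retained needle or a needle-site infection, matter even as single cases. If the threshold were applied, acupuncture would look safer than the observations show.

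**Working it through.** The protocol states no figure that could be reproduced here. The check has two parts.

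**1. The passages side by side**

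| Text | Unit it works on |
|---|---|
| AE definition, 2.13 | Group: four or more participants with the same symptom |
| CRF details and causality, 2.13 | Single event |
| Listed acupuncture events, 2.13 | Single event, no count attached |
| 24 h report, 2.13 | Single event, but only if it is an AE |
| Number, rate and comparison, 2.22 | AEs by the definition |
| Side effects, 2.12 | Any noticed treatment side effect, no count attached |
| 28-day survival, 2.12 | Each participant |

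The phrase "including any undesirable experiences that may occur during the trial period" follows the four-participant condition in the same sentence. It widens the kind of experience covered but does not remove the count. The definition and the single-event procedures cannot both be followed.

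**2. How often a harm would fall below the threshold**

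Inputs: threshold of four participants (2.13); 56 participants, 28 per group (Abstract). The definition does not mention arms, so the count is taken over the whole trial. *Assumption:* per-participant rates of 1% to 10%, because the documents give none, and independence between participants.

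Four participants are 4/56 = 7.1% of the trial, or 4/28 = 14.3% of one arm. Three cases, the most that stay below the threshold, are 3/56 = 5.4% or 3/28 = 10.7%.

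With X ~ Binomial(n, p), the relevant quantity is the chance that the harm occurs but does not qualify:

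P(1 ≤ X ≤ 3) = P(X ≥ 1) − P(X ≥ 4).

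Trials with no case are left out, because reporting none is then correct.

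| p | n | P(X ≥ 1) | P(X ≥ 4) | P(1 to 3) |
|---|---|---|---|---|
| 1% | 28 | 0.245 | 0.0002 | 0.245 |
| 2% | 28 | 0.432 | 0.0022 | 0.430 |
| 5% | 28 | 0.762 | 0.0491 | 0.713 |
| 10% | 28 | 0.948 | 0.3054 | 0.642 |
| 1% | 56 | 0.430 | 0.0024 | 0.428 |
| 2% | 56 | 0.677 | 0.0258 | 0.652 |
| 5% | 56 | 0.943 | 0.3069 | 0.637 |
| 10% | 56 | 0.997 | 0.8240 | 0.173 |

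Differences were taken before rounding. The rows for n = 28 apply to a harm confined to the acupuncture arm; those for n = 56 apply to a harm equally common in both arms, such as itching or dizziness under real or sham needling.

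If one affected participant is enough, the chance that a symptom enters the AE data is the P(X ≥ 1) column. For n = 56 at 5%, that is 94% instead of 31%.

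**The case against.** The strongest defence is that the rest of the protocol treats harms one by one. Section 2.13 names needle-site infection and fainting among the acupuncture events to be reported and attaches no count to them. Section 2.12 records any noticed side effect, and the Abstract says the same. Deaths up to day 28 appear through the survival outcome. Section 2.8 has ICU physicians called at once if acupuncture causes instability. On this view, one badly worded sentence would not stop staff from writing down a single event.

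Most of this stands. A reader might infer that every harm in fewer than four participants, including a death, will be discarded and reported as zero. The documents do not support that: no passage says single events are ignored, and the lines above point the other way.

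A reader might also take the chance of three or fewer cases in 28, which is 1 − 0.305 = 69% at a 10% rate and 1 − 0.049 = 95% at 5%, as the chance of hiding a harm. Those figures include trials with no case at all, apply only to a harm confined to one arm, and rest on assumed rates.

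The defence does not supply what is missing. The side-effect line in 2.12 has no 24 h route and does not reach an event that nobody attributes to treatment, although 2.13 says AEs may be unrelated. The list in 2.13 does not say that a listed event in one participant enters the 2.22 summary. Deaths after day 28 are outside the survival outcome.

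**Conclusion.** The definition is wrong as written and contradicts the individual-level text around it. This is a stated rule, so a separate analysis plan would not excuse it. What the documents support is that a harm in one to three participants has no clear place in the 24 h report or in the AE number, rate and comparison, and that its first case cannot be identified as an AE in time.

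The size depends on assumed rates and on where the harm falls. At 5% it is similar in both settings (71% if confined to 28 patients, 64% across 56). At 10% it falls from 64% to 17% when both arms are affected. These are chances of falling below the stated threshold. They do not show that events would in fact go unrecorded.

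The correction should be made before safety data are summarised, because it is simple and the error favours the treatment.

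**What to change.** - **Section 2.13:** delete the four-participant condition. Define an AE as an untoward occurrence in any one participant during the trial, related or not, and use this for CRF recording and 24 h reporting.
- **Section 2.22:** base the number, rate and any comparison on that definition. If a cut-off is wanted, keep four participants only as a display rule for a summary table, with all events still listed.
- **Section 2.9:** it uses the same term, so check that it reads consistently with the revised definition.
- **Table 1 (secondary):** AEs are marked only at W4 and W12, while 2.13 lets participants report whenever an event occurs. The marks may be meant as end-of-period summaries; reconcile the two.

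The cost is an amendment to the protocol and possibly CRF wording, plus somewhat more AE recording. In ICU patients, where untoward occurrences are likely to be frequent, that extra recording may not be trivial. No additional participants are needed.

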#### 2.2.6. Acupuncture and Sham Therapy

All research assistants and licensed acupuncturists involved in the trial will receive a 2-day training prior to the onset of the study. Both treatments will consist of 20 sessions over 4 weeks, 5 times per week, and each for 30 min. We plan to treat the patients for 4 weeks because normally our patients would have stayed in ICU for 4 weeks. Briefly, patients will be asked to lie down in a supine position. After sterilization, the 0.25 × 40 mm acupuncture needles (Suzhou Tianxie Acupuncture Instruments Co., Ltd., Suzhou, China) will be inserted to the acupoints of the Jianyu (LI15), Quchi (LI11), Zusanli (ST36), Yanglingquan (GB34), and Biguan (ST31) using a neutral reinforcing and reduced manipulation technique. Each needle will be rotated until the patient experiences the “QI” feeling of soreness, heaviness, and the sensation of distension. The procedure for conducting will be standardized as shown in Table 2. Participants in the control group will receive sham needling at the same acupoints with nested blunt needles. All the procedures will remain the same as the one in the treatment group with the exception of the needles, which will be forced to pierce the fixed pad and reach the skin surface without penetrating the skin. All participants will receive regular rehabilitation training.

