### 2.5. Passive and Active Motion of Limb Joints

For the participants in coma or continuous sedation and those with limb muscle strengths < Grade III, a passive motion of limb joints will be performed. If the patient muscle strength is zero, we will help them to passively move each joint in both directions 8 times/group, two groups/exercise, 2 times/day, without half normal ranges of motion. If the muscle strength is Grade I or II, we will move the patient's points 8 times/group in 2 directions, and 2 times/group, 2 times/day, based on a normal range of motion. Conscious patients will be encouraged to exercise according to the following regime: clenched fist and double upper limb lifting exercise, double lower limb flexing 90°, straight leg raising 30°, 2 legs of alternate exercise for 10 min, 3 times/day; every 2 h the patients will be asked to turn over to lie on their sides and then sit upright on the bed (e.g., one end of the bed will be elevated). Patients will also be instructed to maintain the seated position if they can for 20 min, 3 times/day; otherwise, we will raise the head of the bed gradually and let the patients maintain the half-sitting position for 20 min, 3 times/day.

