### 2.14. Follow-Up

The health statuses of the participants after the 4-week treatment period will be followed up on a monthly basis via telephonic and message communications for 3 months based on the previous study for this disease [22]. The symptoms and medication compliance or changes in medication will be recorded. In the event that participants withdrew from the trial or deviated from the intervention protocols, the staff will record the reasons for their withdrawal and the details of their new medications as well as the latest outcome data including the symptoms and frequency of the attacks prior to their exclusion from the study.

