**Figure 2 fig2:**
[figure not shown]
Total study period and evaluation time points.

**Table 1 tab1:** Study design schedule.

Period	Baseline	Treatment (W1–W4)		Follow-up (W12)
Time	W0	W2	W4	W12
Eligibility	X			
Demography and medical history	X			
Physical examination	X			
Informed consent	X			
Quadriceps femoris muscle area	X	X	X	X
Quadriceps femoris muscle thickness	X	X	X	X
Vastus intermediate muscle thickness	X	X	X	X
Subcutaneous tissue thickness	X	X	X	X
Ultrasonic intensity of the rectus femoris	X	X	X	X
MBI	X	X	X	X
MRC	X	X	X	X
Adverse event			X	X
Compliance		X	X	

“X” indicates Yes. MBI: Modified Barthel Index; MRC: Medical Research Council.

**Table 2 tab2:** Acupoints and needle procedure.

Acupoints	Angle and direction	Depth (mm)
Jianyu (LI15)	Straightly	8
Quchi (LI11)	Straightly	8
Zusanli (ST36)	Straightly	13
Yanglingquan (GB34)	Straightly	13
Biguan (ST31)	Straightly	13

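### Table 1 schedules adverse-event assessment only at W4 and W12, and section 2.13 elicits events only by self-report, so transient needling events in weeks 1 to 4 may be missed, especially in patients who cannot communicate

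*Protocol article*

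**What the plan says.** Table 1 ("Study design schedule") has columns W0, W2, W4 and W12. The row "Adverse event" is ticked at W4 and W12 only. W2 is an attended assessment: the five ultrasound measures, MBI, MRC and compliance are all ticked there.

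Section 2.2.6 sets the exposure: "Both treatments will consist of 20 sessions over 4 weeks, 5 times per week, and each for 30 min".

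Section 2.13 says how events come to light: "Participants will be instructed to report any AE to the research team at any time". It then lists what is written on the CRF for each event (including time of occurrence, duration, severity and causality), names the common acupuncture-related events, and requires severe events to go to the safety monitoring board within 24 h.

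On who the participants are, the fifth inclusion criterion in section 2.2.1 reads "5) patients with mechanical ventilation, oxygen concentration", followed by oxygen and pressure limits. Section 2.5 gives instructions that begin "For the participants in coma or continuous sedation".

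For the monthly contacts after treatment, section 2.14 states: "The symptoms and medication compliance or changes in medication will be recorded".

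**The concern.** Section 2.12 lists adverse reactions among the outcomes, section 2.22 provides for a between-group test of AEs, and the Discussion gives safety as an aim. The arms differ in whether the needle penetrates the skin, so minor local events during weeks 1 to 4 are the ones most likely to separate them.

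Those events are often brief. If they are first asked about at W4, they depend on recall, or on a spontaneous report made earlier. A ventilated patient may have difficulty giving such a report, and one in coma or under continuous sedation cannot give it. Two things are then at stake. The count may be incomplete, and whether an event is captured may depend on how awake the participant is. If ability to communicate differed between the arms, the comparison would be biased as well as incomplete.

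**Working it through.** **1. Exposure before the first ticked assessment.** Inputs are from section 2.2.6: 5 sessions per week for 4 weeks.
- Total: 5 × 4 = 20 sessions, which reproduces the stated figure.
- By W2: 5 × 2 = 10 sessions.
- By W4: 20 sessions, the whole course.

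Ten sessions fall before a visit with no AE tick, and all 20 fall before the first visit that has one.

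**2. The Table 1 rows side by side.**

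| Row | W0 | W2 | W4 | W12 |
|---|---|---|---|---|
| MRC | X | X | X | X |
| Compliance | | X | X | |
| Adverse event | | | X | X |

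The gap at W2 is therefore not explained by the absence of a visit.

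**3. How many listed events depend on the patient's account.** Section 2.13 names 14.
- Mainly reported by the patient (8): local skin pain, itching, nausea, severe sharp pain, sharp pain beyond 30 min, numbness, sleeplessness, dizziness.
- Visible to staff (6): ulcers, retained needles, fainting, hematoma, bleeding, infection at the site.

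8 / 14 = 57%. The split is a judgement. Sleeplessness, for example, may be partly observable. For a participant who cannot communicate, self-report yields none of the 14. Observation could yield about 6, provided that someone is asked to record it.

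**4. Which other provisions could fill the gap.**
- Section 2.8: nurses watch ICU patients around the clock and physicians examine them every 6 h. The action stated when acupuncture causes instability is to call the physicians to treat. No AE entry on the CRF is mentioned.
- Section 2.12: side effects that are noticed are recorded. No observer, time or method is named.
- Sections 2.13 and 2.16: these fix what is entered and that CRFs are completed at once. They apply once an event is known.
- Section 2.13, 24 h rule: severe events only.
- Section 2.14: for withdrawals and deviations, staff record reasons and the latest data, including symptoms. Death and discharge before W4 are not mentioned there.

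Together these imply recording throughout the trial, which the two ticks in Table 1 do not show. None of them states an active check during the needling course.

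**5. Size.** The document gives no AE rate, no proportion of participants in coma or sedated, and no reporting sensitivity. The under-count cannot be calculated.

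**The case against.** A reader might infer that AE capture rests on self-report alone and that harms during needling will be under-counted. The document does not support that. ICU monitoring is continuous, section 2.2.6 says patients normally stay in ICU for four weeks, noticed side effects are recorded, CRFs are completed at once, and severe events are reported within 24 h. Staff can see a hematoma or a retained needle without being told. This stands, and it limits the point to transient, non-severe events and to the missing link between monitoring and the CRF.

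The W4 tick sits under a treatment heading that spans W1 to W4 and may mean cumulative collection. That too is fair. Section 2.15 sends the reader to Figure 2 for all time points, and that figure was not available for this review. If recording is meant to be continuous, however, Table 1 should say so.

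A reader might also infer that early leavers go unrecorded and that the monthly contacts ignore AEs. Section 2.14 captures symptoms at withdrawal, and section 2.13 itself defines AEs by symptom, so monthly symptom recording is relevant. Only death and discharge before W4 remain open.

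Ventilation is not the same as inability to report. Section 2.2.6 expects patients to describe the needling sensation, and section 2.4.1 generally requires response to commands for rehabilitation. The number who cannot report is unknown, and nothing shows that it differs by arm.

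Full session forms may well be in the complete protocol or the operating procedures, and their absence from an article is no fault. The point rests instead on the schedule and the method that the article does print.

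Finally, section 2.13 defines an AE as requiring at least four participants with the same symptom. That is a separate cause of under-counting, which the change proposed here would not cure.

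**Conclusion.** The point holds in a limited form. As printed, the AE schedule begins at the end of the 20-session course and skips an attended visit, and the only stated way of eliciting events suits this population badly. It also sits uneasily with the ongoing recording implied by sections 2.12, 2.13 and 2.16. Non-severe, short-lived needling events in weeks 1 to 4 may be missed, and capture may vary with ability to communicate. Bias between arms is possible only if that ability differs between them.

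The conclusion assumes that Table 1 means what it shows and that the ICU monitoring in section 2.8 does not feed the CRF by a route described elsewhere. If the W4 tick is cumulative and the nursing record is already reviewed for AEs, what remains is a correction to the table and one clarifying sentence. Either way the article should be changed. It is a worthwhile improvement to the safety comparison and leaves the efficacy analysis untouched.

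**What to change.** - **Table 1:** tick AEs at W2, or mark them as continuous from the first session to W12, so that the table agrees with sections 2.12, 2.13 and 2.16.
- **Section 2.13:** state that staff already present record AEs on the CRF at each of the 20 sessions, from needle-site inspection and the existing nursing record, adding the patient's own report where the patient can communicate.
- **Ability to report:** note at each check whether the participant could report, so that subjective events can be counted over those able to describe them.
- **Early exits:** record AEs at death or discharge before W4, alongside the withdrawal record already in section 2.14.

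The cost is one short CRF entry per session, at most 20 per participant and 20 × 56 = 1,120 over the planned sample, plus an edit to the table and the text. Reported AE counts are likely to rise, and the report should say that collection was active. No treatment or clinical rule changes.
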